#### Statistical Analysis Plan

A statistical analysis plan was formulated prior to the start of the study. It will be finalized after discussion among the statisticians, principal investigators, and sponsor before database lock. This plan describes only the standard statistical requirements.

Statistical analysis will be conducted using SAS version 9.4. All hypothesis tests will be 2-sided, with a significance level of α=.05. *P* values less than or equal to .05 will be considered statistically significant.

For continuous variables, mean, SD, minimum, maximum, and median values will be used for descriptive statistics. Independent samples *t* tests (for normally distributed data) or Wilcoxon rank-sum tests (for non-normally distributed data) will be used for hypothesis testing. Normality of continuous variables will be assessed using the Shapiro-Wilk test before choosing appropriate parametric or nonparametric tests.

For categorical variables, frequency and percentages will be used for description. Chi-square tests or Fisher exact tests will be used for hypothesis testing. Ordinal variables will be analyzed using the Wilcoxon rank-sum test.

Logistic regression will be used to control for confounding factors affecting the outcome measures. We will also analyze the association between syndrome evolution patterns and therapeutic efficacy. In parallel, multivariate linear regression will be used to explore the relationship between outcomes and potential confounders, such as baseline NIHSS score, study center, age, and sex. For adverse events potentially associated with animal-derived components—including itching, rash, allergic reactions, and gastrointestinal discomfort—we will conduct attribution analysis and report their incidence separately.

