This study aims to evaluate the efficacy and safety of Qizhi Jieyu pill in the treatment of patients during the recovery phase of cerebral infarction through a randomized controlled clinical trial. We hypothesize that the addition of Qizhi Jieyu pill to conventional treatment will result in greater improvement in National Institutes of Health Stroke Scale (NIHSS) scores and lower recurrence rates compared to conventional treatment alone.

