### Outcomes

#### Primary Outcome

The primary outcome is the change in NIHSS score at 48 weeks [21]. This scale evaluates levels of consciousness, command compliance, eye movement, visual field defects, facial paralysis, limb motor dysfunction, ataxia, speech expression, and other parameters.

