#### Secondary Outcomes

The 3 secondary outcomes are the change in TCM syndrome scores, cerebral infarction recurrence rates, and the change in Rankin Scale scores.

A comparison of TCM syndrome scores before and after the medication will be conducted. Based on the guiding principles for clinical research of new Chinese medicines [22], efficacy is categorized as cured, markedly effective, effective, or ineffective according to the change in TCM syndrome scores. TCM symptoms include dizziness, headache, irritability, limb stiffness, neck stiffness, limb numbness, excessive phlegm, shortness of breath, fatigue, spontaneous sweating, dry stool or constipation, dry mouth or thirst, red or dark tongue, and yellow-greasy tongue coating.

In addition, we will use an intelligent TCM diagnostic device (produced by Shenzhen Huiyibida Medical Technology Co, Ltd) to collect tongue images, tongue coating, and pulse information from patients at multiple timepoints. Two study physicians will independently record patients’ clinical symptom information to monitor changes in TCM symptoms and the potential evolution of syndromes.

The cerebral infarction recurrence rate will be evaluated every 12 weeks by CT or MRI and calculated as the number of recurrent cases / the total study population × 100%.

Finally, a comparison of pretreatment and post-treatment Rankin Scale scores will be conducted [23]. The Rankin Scale evaluates neurological recovery after stroke in 6 levels: 0=no symptoms at all, 1=symptoms present but no significant disability, 2=slight disability, 3=moderate disability, 4=moderately severe disability, 5=severe disability, and 6=death.

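### The hypothesis pairs NIHSS with recurrence, but the trial is sized and its primary outcome defined on NIHSS alone, and any P≤.05 counts as significant

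*Protocol article*

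**What the plan says.** All places are in the protocol article.

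- **Hypothesis (end of the Introduction).** Adding the pill to conventional treatment is expected to give "greater improvement in National Institutes of Health Stroke Scale (NIHSS) scores and lower recurrence rates compared to conventional treatment alone". Two outcomes are joined in one statement.
- **Primary Outcome.** There is one: "The primary outcome is the change in NIHSS score at 48 weeks".
- **Sample Size Calculation.** The only inputs are NIHSS change values and their SD. No recurrence rate appears.
- **Secondary Outcomes.** "The 3 secondary outcomes are the change in TCM syndrome scores, cerebral infarction recurrence rates, and the change in Rankin Scale scores". The TCM outcome also has a four-level form: "efficacy is categorized as cured, markedly effective, effective, or ineffective according to the change in TCM syndrome scores".
- **Statistical Analysis Plan.** "All hypothesis tests will be 2-sided, with a significance level of α=.05". P "values less than or equal to .05 will be considered statistically significant". The same section prescribes chi-square or Fisher tests for categorical variables and rank-sum tests for ordinal ones. The primary outcome is a change score, whereas recurrence, the Rankin grade and the TCM efficacy category are of those other kinds. The rule therefore reaches the secondary outcomes.

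**The concern.** The article does not say which result decides the hypothesis. Recurrence has equal standing with NIHSS in the Introduction and is a secondary outcome in the Methods. The significance rule draws no line between the two tiers.

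Suppose the week-48 NIHSS comparison is null and recurrence gives P=.04. As written, the recurrence result is statistically significant and agrees with half of the stated hypothesis. The Discussion (Principal Findings) also counts fewer recurrences among the pill's main advantages, so such a result would probably be presented as efficacy. A lone P≤.05 on the Rankin Scale or the TCM score would likewise be called significant. What is at stake is the conclusion the trial may draw when its primary outcome fails.

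**Working it through.** **1. What the sample size covers.** Inputs from Sample Size Calculation: change of 4.9 in the control group and about 6 in the study group, SD 2.0, α=0.05, β=0.2, stated result 52 per group.

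n = 2σ²(z₀.₉₇₅ + z₀.₈₀)² / δ² = 2 × 2.0² × (1.960 + 0.842)² / 1.1² = 8 × 7.85 / 1.21 = 51.9, so 52.

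The stated 52 is reproduced with δ = 6 − 4.9 = 1.1 and a 2-sided .05. (The difference of 2 printed in the same paragraph would give 16. That is a separate matter.) The whole α of .05 is spent on one NIHSS comparison, and recurrence plays no part.

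**2. Either outcome suffices.** Assume no effect on any outcome and each test at 2-sided .05. For k independent tests:

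- any rejection: 1 − 0.95^k, which is 9.75% for k=2 and 18.5% for k=4;
- a rejection in favour of the pill: 1 − 0.975^k, which is 2.5% for k=1, 4.9% for k=2 and 9.6% for k=4.

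Here k=2 is NIHSS and recurrence. k=4 is the primary and three secondaries, each tested once, with the TCM outcome counted once. The documents give no correlation between outcomes, so it is varied. The rows below the first come from simulating 1,000,000 sets of equally correlated normal test statistics, rejecting beyond ±1.96.

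| Correlation (assumed) | Two outcomes, any | Two, favouring pill | Four outcomes, any | Four, favouring pill |
|---|---|---|---|---|
| 0 | 9.75% | 4.9% | 18.5% | 9.6% |
| 0.3 | 9.5% | 4.8% | 17.5% | 8.8% |
| 0.5 | 9.1% | 4.6% | 15.6% | 7.8% |
| 0.7 | 8.3% | 4.2% | 13.0% | 6.5% |
| 0.9 | 7.0% | 3.5% | 9.4% | 4.7% |

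**3. Sparse recurrence counts.** The table takes each test at its full 5%. With 63 per group and assumed true recurrence rates of 5% to 15%, the chi-square test stays near that (4.7% to 5.1%). Fisher's test rejects only 1.2% to 2.8% of the time. With Fisher and independence, the two-outcome figure becomes 1 − 0.95 × (1 − 0.0115) = 6.1% to 1 − 0.95 × (1 − 0.0275) = 7.6%. The four-outcome figure becomes 15.3% to 16.6%.

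**4. Both outcomes required.** Rejecting both cannot be more likely than rejecting either one alone, so the error is at most 5%. The cost moves to power. The chance of succeeding on both cannot exceed the 80% planned for NIHSS, and it depends on power for recurrence, which the article never considers.

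**The case against.** The strongest reply is that multiplicity rules for secondary outcomes commonly sit in the SAP. The article says of its SAP: "It will be finalized after discussion among the statisticians, principal investigators, and sponsor before database lock", and "This plan describes only the standard statistical requirements". That stands as far as it goes: the absence of an adjustment method from the article is not a fault. It does not answer the point, because the article positively states a two-part hypothesis and a rule covering all tests. An SAP that made the secondaries supportive would have to depart from both.

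A second reply is that a hierarchy exists. One primary outcome is named consistently, the trial is sized on it, and the missing-data rules treat primary and secondary outcomes differently. This is right, and the primary test's error is 5%. What is lacking is any statement of what a secondary result may establish when the primary fails.

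A third reply is that the word joining the two outcomes may mean that both are required. That reading is possible, and under it error is not inflated. The article does not choose.

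A reader might infer more than the documents support:

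- **That the trial's false-efficacy rate is about 16% rather than 5%.** A figure near 16% needs a correlation of roughly 0.4 to 0.5 that nobody states, and it counts rejections in both directions, including against the pill. The article also never claims 5% across all outcomes.
- **That error multiplies over the four visits.** Table 1 schedules measurements at each visit, but nothing says each visit is tested for significance.
- **That the TCM score is wholly unprotected because treatment is open.** Randomization says outcome assessors are blinded, with TCM symptom scores specifically in mind. Symptoms that patients report themselves remain exposed.

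**Conclusion.** The point holds as an inconsistency between the stated hypothesis, the single primary outcome and the uniform significance rule. It is not a defect of the primary test.

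If either hypothesized outcome may carry the claim, any false rejection has a probability of about 7% to 9.8% for the two outcomes and about 9% to 18.5% for four. For four tests, false claims in favour of the pill come to about 5% to 10%, against 2.5% for the primary alone. These figures assume no effect on any outcome, one test per outcome at its full 5%, and a common correlation between 0 and 0.9. Fisher's test on sparse recurrence counts would lower the two-outcome figure further. If both outcomes are required, there is no inflation, but the sample size does not address the joint claim. The wording needs settling under both readings.

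**What to change.** In the Introduction, rest the confirmatory hypothesis on week-48 NIHSS change and give recurrence as a secondary objective.

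In the Statistical Analysis Plan section, replace the uniform rule along these lines: *Only the week-48 comparison of NIHSS change in the full analysis set is confirmatory, at 2-sided .05. Recurrence, Rankin and TCM outcomes are supportive and are reported as estimates with 95% confidence intervals and nominal P values.*

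If formal secondary claims are wanted, use a fixed sequence instead. Week-48 NIHSS is tested first, then one named test per secondary outcome in a stated order, each at .05 and only if every test before it was significant. This holds the family at 5% and leaves the primary sample size unchanged.

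The cost is a few sentences in the protocol and SAP before database lock, with no extra patients or data. The downside is small: an isolated P≤.05 on a secondary outcome, recurrence included, could no longer be presented as proof of efficacy when the primary fails.

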### Sample Size Calculation

The clinical sample size was calculated using a 2-group mean difference test (shown below), where n is the required sample size per group, σ is the pooled SD of the 2 groups, α is the type 1 error, β is the type 2 error, and δ is the expected mean difference between the study and control groups.

Since there are currently no direct data available to calculate the clinical sample size, we mainly referred to 2 clinical studies [15,16]. In these studies, the NIHSS score change value in the control group (conventional treatment) was approximately 4.9. The pooled SD (σ) was estimated based on prior studies that reported SDs ranging from 1.5 to 2.5. We conservatively used σ=2.0 in our calculation to ensure adequate power. It is hypothesized that the change in the study group (conventional treatment plus Qizhi Jieyu pills) would be approximately 6, with a mean difference of 2 between the 2 groups. Assuming a 1:1 sample ratio between the control and study groups with α=0.05 and β=0.2, the required sample size per group is 52. Considering an overall dropout rate of 20%, each group needs 63 participants, for a total of 126 participants. A third-party group composed of experts in TCM, endocrinology, and statistics will be organized at the midterm of the study to reassess the sample size based on the observed effect size of the primary efficacy indicators and associated errors. Figure 1 shows the study flowchart.

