### Randomization

Random numbers will be generated using SAS statistical software (version 9.4), and participants will be assigned to the intervention and control groups in a 1:1 ratio. After screening and informed consent, patients will be randomly assigned to one of the two groups based on their order of enrolment. The drug number for each participant will remain unchanged throughout the study. In the case of a clinical emergency, the participant’s random code and group assignment may be unblinded.

Due to the nature of the intervention, participant and clinician blinding is not feasible. However, outcome assessors will be blinded to group assignments to minimize detection bias, especially for subjective measures such as TCM symptom scores.

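### The primary NIHSS comparison is an unadjusted t test or rank-sum test chosen by a normality pretest, so the effect measure is not fixed in advance and baseline NIHSS is used only for exploration

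*Protocol article*

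**What the plan says.** Under Primary Outcome: "The primary outcome is the change in NIHSS score at 48 weeks". The section Statistical Analysis Plan names no test for this outcome specifically. It gives rules by type of variable. Continuous variables are compared by an independent-samples t test or a Wilcoxon rank-sum test, and the choice is made as follows: "Normality of continuous variables will be assessed using the Shapiro-Wilk test before choosing appropriate parametric or nonparametric tests". For error control: "All hypothesis tests will be 2-sided, with a significance level of α=.05".

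Baseline NIHSS, study centre, age and sex are named once, in this role: "multivariate linear regression will be used to explore the relationship between outcomes and potential confounders". A further sentence reads: "Logistic regression will be used to control for confounding factors affecting the outcome measures". It lists no covariates and no outcome.

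The Sample Size Calculation section uses an unadjusted comparison of two means: "We conservatively used σ=2.0 in our calculation to ensure adequate power", and "Assuming a 1:1 sample ratio between the control and study groups with α=0.05 and β=0.2, the required sample size per group is 52".

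**The concern.** NIHSS change is a continuous variable in the article's scheme, so the general rule decides its primary test. Two things follow.

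**The effect measure is left open.** The trial is sized on a difference in means. A rank-sum test does not estimate that difference unless treatment shifts the whole distribution by a constant. A constant shift is doubtful here, because the inclusion criteria set no NIHSS range and a participant with a low baseline score cannot fall far. NIHSS change is also a whole number, so a normality test can reject because of the scale's coarseness rather than because a t test would mislead. The article does not state the level of the pretest or whether it is applied by arm or to pooled data.

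**Baseline is not used where it could help.** The same floor makes it plausible that change depends on baseline severity. If it does, a baseline-adjusted comparison is more precise and removes chance imbalance in severity. The article already plans a regression with baseline NIHSS and centre but gives it exploratory standing only.

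**Working it through.** **Inputs.** From Sample Size Calculation: σ = 2.0, α = 0.05, β = 0.2, control change 4.9, study-group change 6, a stated difference of 2, 52 per group before dropout, 63 after. Two-sided testing is from Statistical Analysis Plan and 1:1 allocation from Randomization. The correlation r between baseline and week-48 NIHSS, and the two variances, are not given; they are assumptions below.

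**Step 1: reproduce the plan's figure.** n per group = 2(1.960 + 0.842)²σ²/δ².
- δ = 6 − 4.9 = 1.1: n = 51.9, so 52, which matches.
- δ = 2 (as also stated): n = 15.7, so 16, which does not match.

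The calculations below use 1.1. It is an inference from 6 − 4.9 and from the match to 52, since the text also says 2.

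**Step 2: evaluable numbers.** 63 × 0.8 = 50.4, so about 50 per arm if dropouts contribute nothing. The full analysis set keeps anyone with one post-baseline evaluation and carries the last value forward, so the analysed number lies between 50 and 63. Both ends are shown.

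**Step 3: gain from adjusting for baseline.** With equal variances at baseline and week 48, the residual variance after adjustment, relative to the change-score variance, is (1 − r²)/(2(1 − r)) = (1 + r)/2. The residual SD is therefore 2.0 × √((1 + r)/2). Power is from the noncentral t distribution with noncentrality 1.1/(SD × √(2/n)).

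| Analysis | SD | Power, 50 per arm | Power, 63 per arm |
|---|---|---|---|
| Unadjusted | 2.000 | 78% | 87% |
| Adjusted, r = 0.3 | 1.612 | 92% | 97% |
| Adjusted, r = 0.5 | 1.732 | 88% | 94% |
| Adjusted, r = 0.7 | 1.844 | 84% | 91% |
| Adjusted, r = 0.9 | 1.949 | 80% | 88% |

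**Step 4: unequal variances.** If the week-48 SD is k times the baseline SD, the ratio becomes k²(1 − r²)/(1 + k² − 2rk). For k = 1.3 and r = 0.7 this is 0.862/0.870 = 0.991, a gain under 1 point. For k = 1/1.3 and r = 0.7 it is 0.302/0.515 = 0.586, so the gain is larger than under equal variances (0.85). The documents do not say which applies.

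**Step 5: behaviour of the pretest (simulation).** Changes were drawn from a normal distribution with SD 2 and rounded to whole points.
- Shapiro-Wilk at 0.05 rejected in about 38% of single samples of 50 and about 52% of samples of 63. At 52 per arm it rejected in at least one arm in about 63% of trials.
- Type I error of the two-stage procedure was about 0.05 (0.050 to 0.054 across normal, rounded and skewed shapes).
- At a true difference of 1.1 and 50 per arm, power was 0.756 with the pretest, 0.769 for the t test alone and 0.748 for the rank-sum test alone.
- At 52 per arm, the two tests disagreed on significance in about 5% of trials with rounded normal data and up to about 14% with strongly skewed data.

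**The case against.** **The section is generic and a separate plan exists.** It describes itself as covering standard requirements, and the plan is to be finalised before database lock. A full covariate model is something an article may leave to that plan. This is a fair limit. But the pretest and the exploratory standing of the baseline regression are stated, not omitted, and no other rule covers the primary outcome.

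**The pretest does little damage to the error rates.** This stands. A reader might infer that choosing the test from the data inflates the false-positive rate; the simulations show about 5%. The rule is written in advance, so it leaves limited discretion. With skewed scores and a pure shift, the pretest even gained power over the t test, because it moved to the rank-sum test (0.826 against 0.781, and 0.915 against 0.775 in a heavier skew). None of this settles which effect measure is to be reported.

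**The unadjusted test is valid.** This also stands. Randomisation justifies it and it matches the sample-size method. The loss is of precision, not validity.

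**The logistic regression sentence.** It is tempting to read it as a wrong model for a continuous primary outcome. The documents do not support that: the sentence refers to outcome measures in general, recurrence is binary, and linear regression is named separately.

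**Centre.** Nothing in the documents shows that centre predicts NIHSS change. Including it is sensible in a two-centre trial, but no gain can be claimed for it.

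**Conclusion.** The point holds as an improvement to the primary analysis, not as a demonstration of invalid inference. The main harm of the pretest is that the effect measure stays undecided until the data are seen. Its cost in power is about 1 to 2 points when the data are normal apart from rounding.

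Leaving baseline NIHSS out of the primary comparison gives up precision, by an amount the documents cannot fix. Under equal variances, a difference of 1.1 and a change SD of 2.0, the gain runs from about 14 points (r = 0.3) to 2 points (r = 0.9) at 50 per arm, and from about 10 points to 1 or 2 at 63 per arm. It can be under 1 point if variance grows over time. A reader might take the upper end as the expected loss; without a reported correlation or variances, that is not supported. The 63-per-arm figures also assume that carried-forward values have the same SD and treatment effect as observed week-48 values.

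**What to change.** Name one primary analysis: ANCOVA of NIHSS change at week 48 with treatment, baseline NIHSS and centre, reporting the adjusted mean difference with its 95% confidence interval. Remove the Shapiro-Wilk step for the primary outcome and keep the rank-sum test as a prespecified sensitivity analysis.

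The cost is wording in the statistical analysis plan, plus an entry in the registry, where the article says amendments will be recorded. Baseline NIHSS is in the visit schedule and centre is known for every participant, so no new data are needed. This change does not require a larger sample. It should be made before database lock and before outcome data are seen by group.

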## Results

The study was approved by the Ethics Committee of Guang’anmen Hospital, China Academy of Chinese Medical Sciences, on March 3, 2025 (2025-025-KY-01), and was registered on the International Traditional Medicine Clinical Trial Registry on April 6, 2025 (ITMCTR2025000653), and any potential protocol amendments will be recorded there. Participant screening began on April 10, 2025, with enrolment expected to be completed by December 31, 2025. The final study results are planned to be published by December 31, 2026.

This study aims to evaluate the efficacy and safety of Qizhi Jieyu pill in the treatment of patients in the recovery phase of cerebral infarction, providing a treatment option supported by high-quality, evidence-based medicine for the clinical management of recovery phase cerebral infarction.

